### Aims

To pilot the feasibility of a brief intervention in stroke patients exhibiting sub-optimal adherence with the aim of:

(a) establishing a better medication taking routine using an implementation intentions intervention

(b) eliciting and modifying any emergent erroneous beliefs regarding the patient's medication and their stroke.

We will test whether medication routines and beliefs are changeable, and if the results are promising, this will pave the way for a larger randomised controlled trial (RCT) to determine whether adherence is improved, physiological risk is changed (e.g. via reduction in blood pressure), and rate of recurrent vascular events is reduced.

### Research questions

(a) Is the brief intervention feasible, understandable and acceptable (e.g. regarding uptake/attrition)?

(b) Does the intervention improve adherence?

(c) Is improvement in adherence mediated by (i) changes in illness and medication beliefs and/or (ii) reduced forgetting?

(d) What effect size is observed to inform the power calculation for a larger, more definitive study?

## Methods/Design

### Recruitment

In order to maximise recruitment and the representativeness of the sample, we shall attempt to recruit and obtain consent from consecutive patients who are discharged from the Edinburgh Western General Hospital stroke units and clinics and who are prescribed secondary antihypertensive medication. Our previous experience suggests that this approach will significantly improve trial recruitment. Currently approximately 300 in-patients and 400 out-patients are discharged per year, with over 60% prescribed antihypertensive medication. We will screen 400 first-time stroke (ischaemic and haemorrhagic) or Transient Ischaemic Attack (TIA) patients, and expect a 75% response rate (300). We plan to include both stroke and TIA patients since both groups of patients are treated in a similar way with secondary prevention drugs and are likely to have similar issues with respect to non-adherence [9]. We have decided to focus on the early months following stroke in order to maximise the likelihood of preventing a further stroke. Poor adherence will have a much greater effect on stroke risk in the first few months because the risk of stroke (and thus the absolute risk reductions associated with drug treatment) is highest at this stage [19]. Furthermore, following Petrie et al. [20], we believe that the efficacy of the intervention will be enhanced by eliciting and correcting dysfunctional stroke and medication beliefs soon after preventative drugs are started. However, we have to strike a careful balance between early intervention, and also allowing enough time for participants to demonstrate variance in adherence, so that we can specifically target those showing sub-optimal adherence, thus our decision to assess adherence at 3 months post stroke or TIA. Consenting participants will therefore be contacted by post 3 months after their event and asked to complete the Medication Adherence Self Report Scale (MARS) [21] and return it in a stamped addressed envelope. In this mailing, we will also ask participants to complete the Brief Illness Perceptions Questionnaire [22] and the Beliefs about Medication Questionnaire [23]. This will allow us to economically test the robustness and replicability of the association we previously observed between specific medication concerns and self-reported adherence in a new large sample of TIA/stroke patients. We will then invite all those reporting sub-optimal adherence on the MARS (score of 24 or less) to participate. Based on our earlier study we conservatively estimate that approximately 30% will report some degree of poor adherence, and of those, up to 30% may then decline to participate. We therefore estimate that if we invite 90 patients, 60 will agree to participate. They will then be randomly allocated to brief intervention or treatment as usual (TAU). We are allowing for a further 10% attrition rate during the trial, however, one of the main purposes of this pilot is to obtain data on uptake, acceptability and attrition.

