**Methods/Design:**

Thirty patients will be allocated to a brief intervention (2 sessions) and 30 to treatment as usual. The primary outcome will be adherence measured over 3 months using Medication Event Monitoring System (MEMS) pill containers which electronically record openings. Secondary outcomes will include self reported adherence and blood pressure.

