### Analysis

MEMS data will be analysed using an intention to treat protocol in a repeated-measures mixed-design (2 groups * 3 time points). One of the primary aims of this pilot study is to determine the effect size achieved by this pilot to inform the sample size calculation for a larger, more definitive multi-centre study. (We acknowledge that the effect size observed may differ from what one would see in a large trial, however, the effect size sought in the large trial should be within the 95% CI of the estimate derived from this pilot. The pilot will thus give a useful measure of the variability of the primary outcome measures). Using G-Power [28] for this pilot, we calculate that with 2 arms of 30 participants, focusing on the treatment group by time interaction term, we should be able to detect an effect size of 0.2, with a power of 0.80 and alpha set at 0.05 (i.e. a 0.2 of a standard deviation improvement in the brief intervention arm in number of days per month that the correct antihypertensive medication is taken, relative to the TAU arm).

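### The stated 10% attrition allowance enters neither the number randomised nor the power figure, which is given for 60 patients although the plan expects about 54

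*Protocol article*

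**What the plan says.** The Recruitment section sets out how patients reach randomisation. Of those reporting poor adherence, "up to 30% may then decline to participate". It continues: "We therefore estimate that if we invite 90 patients, 60 will agree to participate. They will then be randomly allocated". It then adds: "We are allowing for a further 10% attrition rate during the trial". The same sentence notes that measuring attrition is itself a main purpose of the pilot.

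The Abstract (Methods/Design) fixes the allocation: "Thirty patients will be allocated to a brief intervention (2 sessions) and 30 to treatment as usual".

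The Analysis section bases its power statement on the same number: "we calculate that with 2 arms of 30 participants, focusing on the treatment group by time interaction term", and "we should be able to detect an effect size of 0.2, with a power of 0.80 and alpha set at 0.05". It explains the effect size as "a 0.2 of a standard deviation improvement in the brief intervention arm in number of days per month". It states neither the correlation between the monthly measurements nor any sphericity correction. It describes the MEMS analysis as intention to treat in a two-group, three-time-point repeated-measures mixed design, and it names no estimation method.

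**The concern.** An allowance for attrition normally shows in one of two places. Either more patients are randomised than the calculation needs, or the calculation uses the smaller number expected to remain. Here the number randomised and the number powered are both 60, so the sentence claiming an allowance has no counterpart in the figures. The loss is described as further and as occurring during the trial, so it is separate from the refusals before randomisation.

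At stake is a power figure quoted for more patients than the plan expects to keep. The pilot's effect size and its 95% confidence interval are also meant to inform the sample size of a larger trial, so the expected precision should likewise refer to the patients who will supply data.

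**Working it through.** **Inputs from the article.** Randomised: 60, 30 per arm (Abstract; Recruitment). Loss during the trial: 10% (Recruitment). Effect size 0.2, power 0.80, alpha 0.05, group-by-time interaction, 2 groups and 3 time points (Analysis).

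**Assumptions not in the article.** Correlation ρ between months, varied. Sphericity (ε = 1) unless stated. Effect size 0.2 read as Cohen's f.

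**Step 1: head count.**
- Expected to remain: 60 × 0.9 = 54, or 27 per arm.
- Needed to keep 60 after a 10% loss: 60 / 0.9 = 66.7, so 67 randomised.
- Recruitment funnel: 400 × 0.75 = 300; 300 × 0.30 = 90 invited; 90 × 0.70 = 63. Even if all 63 were randomised, 63 × 0.9 = 56.7. The gap between 63 and 60 arises before randomisation and does not cover the later loss.

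**Step 2: the plan's own figure.** For the interaction test, the noncentral F distribution has λ = f² × N × m × ε / (1 − ρ), with df1 = (k − 1)(m − 1)ε and df2 = (N − k)(m − 1)ε, where k = 2 and m = 3. At N = 60 and f = 0.2:
- ρ = 0.5: λ = 0.04 × 60 × 3 / 0.5 = 14.4, df 2 and 116, power 0.93.
- ρ = 0.272: λ = 7.2 / 0.728 = 9.89, power 0.80.

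So 0.80 is exact for 60 only at a correlation of about 0.27. Because no correlation is given, the stated figure cannot be reproduced uniquely.

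**Step 3: the same test at N = 54.** At ρ = 0.272, λ = 0.04 × 54 × 3 / 0.728 = 8.90, df 2 and 104, power 0.75.

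| ρ (assumed) | Power, N = 60 | Power, N = 54 |
|---|---|---|
| 0 | 0.66 | 0.61 |
| 0.2 | 0.76 | 0.71 |
| 0.27 | 0.80 | 0.75 |
| 0.3 | 0.82 | 0.77 |
| 0.4 | 0.87 | 0.83 |
| 0.5 | 0.93 | 0.90 |
| 0.6 | 0.97 | 0.95 |

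The loss is about 2 to 5 points over this range. Power at 54 equals 0.80 at ρ = 0.347 and is higher above it. That threshold assumes sphericity: with ε = 0.75 and ρ = 0.5, power is 0.86 at 60 and 0.82 at 54. The f detectable with power 0.80 rises from 0.200 to 0.211 at ρ = 0.272, and from 0.166 to 0.175 at ρ = 0.5.

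**Step 4: precision.** For a difference between arms in one month, in SD units, the approximate 95% half-width is 1.96 × √(2/n). With n = 30 it is 1.96 × 0.258 = 0.51. With n = 27 it is 1.96 × 0.272 = 0.53. The ratio is √(30/27) = 1.054, so the interval is about 5% wider.

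**Step 5: the article's own gloss.** If 0.2 is instead a difference of 0.2 SD between arms, a simple two-mean comparison has power of about 0.12 with 30 per arm and 0.11 with 27. Attrition matters little on that reading. It shows why a restated figure must also define the effect size.

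**The case against.** The strongest reply is that the consequence is small and may be nil for the 0.80 figure. A reader might infer that the stated 80% power fails under the plan's own attrition. The article does not support that. With f = 0.2, sphericity and a correlation of 0.5, 42 patients already give 0.80 and 54 give 0.90. The value of 0.27 is obtained by working backwards so that 60 gives exactly 0.80, and the article does not state it. This reply stands: power falls below 0.80 only if the correlation is under about 0.35, again with sphericity.

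A reader might also infer that the planned analysis drops anyone with a missing month and so contradicts intention to treat. That is not shown either. The Analysis section names neither ANOVA nor complete-case deletion. Its wording describes a design, which a likelihood-based mixed model fits equally well, and a planning calculation in G-Power does not fix the estimation method. Rules for missing months may sit in an analysis plan that is not shown, so their absence here is no finding.

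Two further replies have weight. The pilot is meant to measure attrition, so 10% is only a working figure. And under a model that uses partial data, patients who leave late still contribute, so 27 per arm is a cautious basis. Neither reply explains where the claimed allowance enters the figures.

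**Conclusion.** The point holds as a mismatch between a stated allowance and the figures. The 10% enters neither the 60 randomised nor the 30 per arm used for power, and the plan's own rate leaves about 54. This part needs no assumption beyond the article's numbers.

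The size is modest: about 2 to 5 points of power for f = 0.2 at correlations from 0 to 0.6 with sphericity, and about 5% on the width of a confidence interval. Whether power at 54 is below 0.80 depends on a correlation the article does not give. A correction is still worthwhile, because the plan chose to state a power figure and it should refer to the number expected to contribute data.

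**What to change.** Restate the power and the expected precision for 27 analysed per arm. Give the assumed correlation between months and say whether 0.2 is Cohen's f or a difference in standard deviations. Alternatively, remove the statement that attrition is allowed for and say plainly that the power figure assumes all 60 are analysed. The cost is a sentence or two and possibly a slightly less favourable figure, with no change to recruitment or design.

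As an optional safeguard, name a likelihood-based mixed model that uses every recorded month from all randomised participants, which guards against losing patients who have one month missing. This costs one sentence and does not correct a stated error.

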
#### Inclusion criteria

We aim to be as inclusive as possible and recruit all patients who had their first ischaemic or haemorrhagic stroke or TIA 3 months earlier and were discharged from the ward or clinic on any secondary preventative medication and are living at home.

#### Exclusion criteria

We will only exclude people who are not on anti-hypertensive medication 3 months after their stroke/TIA, or whose degree of aphasia (Frenchay screen <13/20) or MMSE <23 makes completion of the study measures not feasible. Those who report already using Dosette boxes to improve their adherence, or are not responsible for taking their own medication, will also be excluded.

### Design

A pilot RCT with patients allocated to intervention versus treatment as usual (TAU). Web-based randomisation at the patient level into intervention or TAU will be provided by the Edinburgh Clinical Trials Unit, using minimisation with a random element to ensure that the two trial arms are not significantly different on three key variables: age, number of pills taken per day and baseline MARS adherence. A CONSORT flowchart of the trial design is shown in Figure 1.

**Figure 1 F1:**
[figure not shown]
**CONSORT flowchart of trial design**.

### Setting

A single-centre trial at a large teaching hospital in Scotland.

### Ethical Approval

Ethical approval has been granted by Lothian NHS Board, South East Scotland Research Ethics Committee (REC ref. no. 09/S1102/36).

### Measuring Adherence

There is no agreed "gold standard" when measuring adherence [21]. Our previous study clearly established that assay of urinary aspirin levels in stroke patients lacked sensitivity and was unhelpful [15]. Garber et al. [24] showed that appropriately framed self-report questionnaires show good concordance with electronic cap monitors and blood and urine measurement. The MARS attempts to reduce social desirability effects by framing questions so to make non-adherent responses socially acceptable. The MARS has high internal and test-retest reliability, and has been shown to predict clinical outcome (blood pressure within range [21]). We used the MARS as our primary outcome measure in our previous study, establishing that stroke patients found it easy to use and understand, and we demonstrated that MARS scores were not correlated with a social desirability measure but were prone to ceiling effects [15]. We will therefore use the MARS as a viable and economic screen for patients demonstrating sub-optimal adherence, but will then use MEMS (Medication Event Monitoring System, MEMS^® ^Aardex Ltd, Switzerland) pill containers which electronically record openings as our primary outcome measure in the evaluation of this pilot RCT.

### Intervention

Two brief sessions, two weeks apart with a trained Research Fellow, lasting approximately 30-45 minutes each. Participants will be given the choice of having home visits or coming into a local hospital-based Clinical Research Facility.

***Session 1 ***will focus on helping each patient draw up a specific plan, so as to establish a better medication-taking routine using an implementation intentions approach. Patients will be helped to complete an individualised worksheet plan for each scheduled daily dose of antihypertensive medication, following Brown et al. [17]. The participant and Research Fellow will both keep a copy of the plan. Baseline blood pressure readings will also be taken during Session 1.

***Session 2***. The effectiveness of the implementation intentions plan and any barriers/difficulties in following the plan will be reviewed in session 2, with individually-tailored coping strategies/plans developed collaboratively, following the methods outlined by Sniehotta et al. [25]. This session will also focus on eliciting and, if appropriate, challenging patients' beliefs regarding their medication, e.g. beliefs regarding toxicity, dependence, fears regarding medications interacting harmfully etc., using the participants' responses on the BIPQ and the BMQ as a basis. The aim here will be to correct any misperceptions and provide evidence so that participants' medication **necessity **beliefs come to outweigh their medication **concerns **beliefs. Previous work has demonstrated that better adherence results when medication necessity beliefs outweigh concerns [14]. Modification of erroneous beliefs about stroke will be based on the model of Petrie et al. [20] who elicited and modified patients' dysfunctional beliefs regarding their recent myocardial infarction. This resulted in faster return to work and lower angina symptoms at 3 months. If the Research Fellow is unable to answer any specific questions regarding the patient's stroke or medication, then immediately following the interview, the RA will email the query to one of the stroke consultant experts on the research team, and the RA will then telephone the patient with the information within 7 days of the interview. At the end of session 2, the Research Fellow will fill each participant's MEMS medication bottle with the following month's supply of antihypertensive medication. (We propose using the patients' existing supply of antihypertensive medication. A check will be taken at session 1, and if supplies are running low, participants will be asked to obtain their repeat prescription in advance of session 2). For each of the next three months (Sessions 3-5), the Research Fellow will repeat this process, and also take an electronic reading from the MEMS cap, downloading the data on to a laptop PC for later analysis. At the first of these follow-up visits (Session 3), participants will again complete the Brief Illness Perceptions Questionnaire (BIPQ) [22] and the Beliefs about Medications Questionnaire (BMQ) in order to test whether the intervention has resulted in changes to stroke and/or medication beliefs [23]. At the final visit, at 3-month follow-up (Session 5), the outcome measures will be administered.

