### Primary outcomes

Medication adherence will be recorded using MEMS (Medication Event Monitoring System, MEMS^® ^Aardex Ltd, Switzerland) pill containers which electronically record openings. Following Brown et al. [17], and in line with previous studies using this method, we shall use the following main outcomes, counting each opening as a presumptive dose: (a) percentage of doses taken (versus doses prescribed), (b) percentage of days on which the correct number of doses was taken, and (c) percentage of doses taken on schedule. Again, following Brown et al. [17], we designate doses as having been taken on schedule if the MEMS bottle was opened within a 3-hour (plus or minus) time window for each dose. The electronic monitoring caps can be connected to a personal computer that reads the data from the pill caps' microprocessors and generates a printout of every pill bottle opening over an extended time period (in this case, the preceding month). Because patients will usually be on a variety of medications, we will target antihypertensive medication for MEMS measurement, particularly as there is clear evidence regarding poorly treated blood pressure significantly increasing the risk of future vascular events, and as stated in the introduction, it is estimated that only 30-50% of patients regularly take their antihypertensive drugs as prescribed [2]. If patients are taking more than one antihypertensive, we shall target the drug that is taken most frequently. MEMS have been successfully used in a variety of medication adherence interventions e.g. Brown et al. [17]. However, as with most methods in this area, MEMS measurement is not immune from the Hawthorne effect, i.e. medication-taking behaviour is often improved in the short-term as a direct consequence of it being measured [26]. We shall therefore use MEMS containers to record medication taking in both intervention and control arms for 3 months. We predict in the control arm that adherence will gradually drop off over the 3 months (as the Hawthorne effect fades), whereas there will be an increase or no change over the 3 months in the intervention arm. A recent three-month RCT aimed at improving adherence to medication in HIV-affected individuals also used this MEMS evaluation of outcome, and in the intention to treat analysis showed no change in the TAU arm, but a significant improvement in the psychological intervention arm, with a controlled effect size of 1.0 [27]. We acknowledge the limitation in this pilot that the Research Fellow will not be blind to treatment arm; however, as our primary outcome is MEMS automated recording of days per month that the correct dose of hypertensive was taken, the potential for bias is significantly reduced.

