### Evaluation

The effects of the intervention will be evaluated in all participants via measurement of the primary and secondary outcome variables listed above. The Research Fellow will also take baseline and 3-month follow-up blood pressure measurements using an OMRON M10-IT BP monitor following a standardised protocol (mean of 3 recordings). The blood pressure results will be fed back to the participants and their GPs in both intervention and TAU arms, together with simple information regarding ideal values. (NB we do not expect significant change in these physiological variables in this pilot, but these may change - albeit over a longer time period - in a larger trial and we wish to assess feasibility and patient acceptability). On completion, patients in the intervention arm only will also take part in a brief semi-structured interview to assess their views regarding the intervention. They will also be asked to complete Likert-type scales assessing (a) ease of understanding, (b) acceptability and (c) perceived benefit for each of the intervention components, namely, 1) medication routine planning worksheet, 2) discussion/information regarding medication, 3) discussion/information regarding stroke, and 4) blood pressure measurement. Additional file 1: Table S1 details all patient contacts and assessments at each time point.

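### Follow-up belief questionnaires and MARS are completed at visits run by the unblinded Research Fellow who delivered the intervention, so these self-report contrasts could favour it

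*Protocol article*

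**What the plan says.** All references are to the protocol article.

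- **Who delivers the intervention.** The Intervention section specifies "Two brief sessions, two weeks apart with a trained Research Fellow". In Session 2 the Fellow takes the patient's BIPQ and BMQ answers as the starting point for challenging beliefs, so that perceived necessity comes to outweigh concerns.
- **Who runs follow-up.** The same section continues: "For each of the next three months (Sessions 3-5), the Research Fellow will repeat this process". The Timetable confirms that all five contacts are face to face.
- **What is collected then.** Participants complete the BIPQ and BMQ again at Session 3. For the last visit the text reads "Session 5), the outcome measures will be administered". MARS is the first of the two listed secondary outcomes.
- **How baseline was collected.** Recruitment has participants complete MARS by post "and return it in a stamped addressed envelope", with the BIPQ and BMQ in the same mailing.
- **Blinding.** Under Primary outcomes: "We acknowledge the limitation in this pilot that the Research Fellow will not be blind to treatment arm". Because the primary outcome is recorded automatically, the protocol concludes that "the potential for bias is significantly reduced".
- **Control arm.** Controls have the same number of visits, the same questionnaires and the same timing. Their first two sessions are filled with conversation unrelated to medication.
- **Acceptability.** Under Evaluation, intervention patients alone are interviewed and rate "ease of understanding, (b) acceptability and (c) perceived benefit for each of the intervention components". The person who collects these ratings is not named.

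**The concern.** The argument that automated recording limits bias holds for MEMS and stops there. MARS, BMQ and BIPQ are the participant's own report, completed at a visit run by the person who coached that participant. An intervention patient has heard from the Fellow which beliefs about medication are regarded as mistaken. About a month later the same patient fills in the same belief instruments at the Fellow's visit. A control patient has had no such conversation in Sessions 1 and 2. The pressure to give the expected answer could therefore differ by arm.

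These measures matter to the pilot. Research question (c) asks whether any gain in adherence is mediated by changed beliefs, Process evaluation names the BMQ and BIPQ as the mediators, and the Aims make changeability of beliefs part of what would lead to a larger trial. MARS is a secondary outcome.

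**Working it through.** **Step 1. Set each measure against the stated safeguard.**

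| Measure | Baseline | Follow-up | Covered by automated recording? | Control comparison? |
|---|---|---|---|---|
| MEMS (primary) | none before Session 2 | electronic, monthly download | Yes | Yes |
| BMQ, BIPQ | postal | Session 3 visit | No | Yes |
| MARS | postal | Session 5 visit | No | Yes |
| Acceptability and perceived benefit | none | on completion, collector not named | No | No, intervention arm only |

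The protocol refers to the Research Fellow in the singular, so I read the person at Sessions 3 to 5 as the one who delivered Sessions 1 and 2.

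**Step 2. Separate what differs by arm from what does not.**

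- The move from postal to visit completion applies to both arms. By itself it confounds change from baseline within an arm, but not the randomised contrast. It would affect the contrast only if it acted differently in coached patients.
- Having one's answers challenged by the Fellow happens only in the intervention arm. This is the route by which the contrast could be biased, and it is most direct for BMQ and BIPQ.
- A reporting shift would inflate the arm-to-belief path of the mediation analysis. Its net effect on the estimated mediated effect is less certain, because belief scores altered by expectation may relate less closely to MEMS adherence.

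**Step 3. Illustrate the size.** No figure in the document is at issue, and none allows the bias to be estimated. The shift b is purely an assumption. Take a two-sample t test, two-sided alpha 0.05, true effect zero, and a shift of b SD towards the intervention:

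- noncentrality = b / √(2/n), with 2n − 2 degrees of freedom;
- n = 30 per arm (Analysis section): √(2/30) = 0.258, so b = 0.2 gives 0.2 / 0.258 = 0.775 and b = 0.3 gives 1.162;
- n = 27 per arm, after the 10% attrition allowed for under Recruitment (30 × 0.9 = 27): √(2/27) = 0.272, so b = 0.2 gives 0.735.

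The probability of a significant result favouring the intervention is:

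| Assumed shift (SD) | 30 per arm | 27 per arm |
|---|---|---|
| 0 | 2.5% | 2.5% |
| 0.1 | 5.7% | 5.5% |
| 0.2 | 11.5% | 10.8% |
| 0.3 | 20.7% | 19.0% |
| 0.5 | 47.8% | 43.8% |

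The first row is also the case of a mode change acting equally in both arms: the two-sided error rate stays at 5%.

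**The case against.** The other side has several good points.

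- **The limitation is admitted and the primary outcome is automated.** This stands. The point concerns secondary, process and feasibility measures only.
- **MARS is built to resist social desirability.** The Measuring Adherence section says its wording makes non-adherent answers acceptable, and that earlier scores did not correlate with a social desirability measure. This is partial reassurance. The earlier work is presented as a study of determinants, with no coaching by the data collector described, and it says nothing about BMQ, BIPQ or the acceptability scales.
- **Controls also meet the Fellow monthly.** They have MEMS downloads too, and the non-medication conversation is limited to the first two sessions. They may also wish to look adherent, so the asymmetry is smaller than it first appears. It does not vanish, because only intervention patients had their stated beliefs challenged.
- **Administering a form at a visit does not exclude self-completion.** True, and handling details may sit in the full protocol or the supplementary table. The article does not describe any privacy from the Fellow.
- **Sessions are audio-recorded.** The stated purpose is supervision and treatment fidelity. Recording might restrain prompting by the Fellow, but does not change what a participant wishes to report.
- **Postal return could lose data.** Recruitment expects 75% to respond. If follow-up returns were similar, 25% of 60 = 15 would be missing, against 6 under the planned 10% attrition. This is a sound reason to prefer sealed completion at the visit.

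A reader might go further and infer that the self-report results will certainly favour the intervention, that the change of mode biases the comparison between arms, or that the Fellow is known to collect the acceptability ratings. The documents support none of these: they show a risk rather than a realised bias, the mode change is shared by both arms, and the collector is not named. Nor should an assumed shift be set against the 0.2 SD in the Analysis section, which concerns days of correct antihypertensive intake and not MARS or BMQ.

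**Conclusion.** The point holds as a risk of bias outside the primary outcome. The fact that "the Research Fellow will not be blind to treatment arm" is defended only for MEMS, while BMQ and BIPQ at Session 3 and MARS at Session 5 are completed at that Fellow's visits. The between-arm contrasts on these measures could favour the intervention, most plausibly for the belief mediators. The acceptability ratings have no control comparison; they could be too favourable if the Fellow collects them, which is an inference.

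The size is unknown. Under the assumed shifts of 0.1 to 0.3 SD, the chance of a false result in the intervention's favour would be about 6% to 21% with 30 per arm, in place of 2.5%. This rests on the same person running all sessions and on no undisclosed arrangement for private completion. It is a cheap improvement and not a fault that undermines the trial.

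**What to change.** At Sessions 3 and 5, have participants in both arms complete the scheduled questionnaires (BMQ and BIPQ at Session 3, MARS at Session 5) privately and seal them in an envelope labelled with study number only. Treat the acceptability scales in the intervention arm the same way. Someone other than the Research Fellow, such as existing trials unit or data staff, should open and score them. Report these outcomes as self-report by participants who know their allocation, and do not interpret within-arm change from the postal baseline without noting the change of setting.

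The cost is envelopes, a line in the procedures and a slight handling burden, with no additional staff. A few forms may be incomplete, because the Fellow cannot check them. Handing the pack over at the visit should avoid most of the loss expected from postal return. The change reduces the Fellow's influence on the answers; it cannot remove participants' own knowledge of what they were taught.
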